## Abstract

**Introduction:**

Oligodendroglioma (ODG) is a rare type of brain tumour, typically diagnosed in younger adults and associated with prolonged survival following treatment. The current standard of care is maximal safe debulking surgery, radiotherapy (RT) and adjuvant procarbazine, lomustine and vincristine (PCV) chemotherapy. Patients may experience long-term treatment-related toxicities, with RT linked to impairments of neurocognitive function (NCF) and health-related quality of life (HRQoL). With proton beam therapy (PBT), radiation dose falls off sharply beyond the target with reduced normal brain tissue radiation doses compared with photon RT. Therefore, PBT might result in reduced radiation-induced toxicity compared with photon RT.

**Methods and analysis:**

APPROACH is a multicentre open-label phase III randomised controlled trial of PBT versus photon RT in patients with ODG, investigating the impact of PBT on long-term NCF measured using the European Organisation for Research and Treatment of Cancer (EORTC) Core Clinical Trial Battery Composite (CTB COMP). The trial will randomise 246 participants from 18 to 25 UK RT sites, allocated 1:1 to receive PBT or photon RT, with PBT delivered at one of the two UK PBT centres. Participants with grade 2 and grade 3 ODG will receive 54 Gy in 30 fractions and 59.4 Gy in 33 fractions, respectively, followed by 6×6-weekly cycles of PCV chemotherapy. The trial contains staged analyses, with an internal pilot for feasibility of recruitment at 12 months, early assessment of efficacy at 2 years, futility assessment and final primary endpoint comparison of NCF between arms at 5 years. Secondary endpoints include additional NCF, treatment compliance, acute and late toxicities, endocrinopathies, HRQoL, tumour response, progression-free survival and overall survival.

**Ethics and dissemination:**

Ethical approval was obtained from Newcastle North Tyneside REC (reference 22/NE/0232). Final trial results will be published in peer-reviewed journals and adhere to International Committee of Medical Journal Editors (ICMJE) guidelines.

**Trial registration number:**

ISRCTN:13390479.

STRENGTHS AND LIMITATIONS OF THIS STUDYUK multicentre phase III randomised controlled trial of proton beam therapy versus photon radiotherapy for oligodendroglioma.Multistaged analyses will provide continuous assurance of trial processes to ensure successful trial delivery, including preplanned interim analysis to enable early assessment of benefit from proton beam therapy versus photon radiotherapy.Trial endpoints and trial design informed by patient and public involvement, with strong emphasis on participant-centred outcome measures.Embedded mechanistic component to explore relationships between spatial location of radiation dose to brain substructures and development of neurocognitive toxicities.

## Introduction

 Oligodendroglioma (ODG) is rare, accounting for around 3% of new brain tumour diagnoses with approximately 350 patients diagnosed each year in the UK.^1^ The diagnosis of ODG is determined by the presence of 1p19q chromosomal codeletion and isocitrate dehydrogenase (IDH) mutation,^2^ with histological classification as either WHO grade 2 or 3. ODG typically has a good prognosis, with median survival in excess of 10 years, and median age at diagnosis is approximately 45 years.^3^,^6^ The majority of tumours are located in higher functioning regions of the brain in the frontal or temporal lobes. The current standard of care is maximal safe debulking surgery, radiotherapy (RT) and adjuvant procarbazine, lomustine and vincristine (PCV) chemotherapy.^3 7 8^

Photon RT is typically used to treat ODG, but it may be associated with irreversible long-term toxicities including impairment of neurocognitive function (NCF).^9^,^11^ A recent Cochrane systematic review of long-term neurocognitive changes after photon RT for gliomas concluded that the magnitude of impact on NCF following RT remained uncertain, given the paucity of data and risk of bias inherent in the published literature.^11^ Nevertheless, treatment-related toxicities have the potential to impact on all aspects of life, including daily functioning, work, education, relationships and caring responsibilities, especially given the relatively young age and prolonged survival of many patients with ODG.^12^ In addition, even small deficits in NCF may negatively impact health-related quality of life (HRQoL) and affect activities of daily living.^13^

It is hypothesised that proton beam therapy (PBT) may result in fewer long-term toxicities compared with photon RT due to relative sparing of surrounding normal brain structures, which could result in less neurocognitive decline. In silico studies in patients with low-grade gliomas have demonstrated dosimetric advantages of PBT (see figure 1), but there remains an absence of high-level evidence that demonstrates clinical improvements in long-term toxicity using this approach.^14^ The outcomes of small, single-arm prospective cohort studies with relatively short follow-up in low-grade glioma suggest that stability in NCF and HRQoL may be achieved after PBT.^15^,^17^ However, there is an urgent need for randomised controlled trials (RCTs) to definitively characterise the clinical benefits of PBT compared with photon RT.

**Figure 1 F1:**
[figure not shown]
Photon RT and PBT radiotherapy dose distributions in a patient treated for ODG. Planning CT axial images of the brain showing radiation dose distributions for corresponding photon RT and PBT plans. In each plan, the dark blue contour represents the Planning Target Volume (PTV). The isodose lines represent the radiation dose to be delivered as a percentage of the prescription dose, as indicated in the key; warmer colours/higher percentages represent regions of higher dose. Greater dose sparing of normal brain structures outside of the PTV is apparent in the PBT plan. It is currently uncertain if this translates into a clinical improvement in neurocognitive function. ODG, oligodendroglioma; PBT, proton beam therapy; RT, radiotherapy.

A recent systematic review highlighted the limited current evidence base for PBT, with a need for prospective randomised trials to evaluate its benefits in terms of long-term toxicities and patient-reported outcomes.^18^ PBT is now available in two UK National Health Service (NHS) centres (The Christie NHS Foundation Trust and University College London NHS Foundation Trust), which provides an opportunity to develop a practice-changing evidence base for PBT.

## Methods and analysis

### Study design

APPROACH: Analysis of Proton versus Photon Radiotherapy in Oligodendroglioma and Assessment of Cognitive Health is a multicentre open-label parallel group phase III RCT of PBT versus photon RT in patients with ODG. The aim of the study is to determine whether participants treated with PBT demonstrate better NCF compared with those treated with photon RT. A mechanistic component will investigate the relationship between RT dosimetry in specific brain regions and impairments in NCF.

Participants are patients with ODG who require RT, followed by adjuvant PCV chemotherapy, and who meet all eligibility criteria for the study (inclusion and exclusion criteria are listed in table 1), and their caregivers. Potential participants will be identified at local neuro-oncology multidisciplinary team meetings, approached at outpatient clinics and provided with the study Participant Information Sheet. Patients will be given time to consider participation. Written informed consent will be obtained. Participants will be randomised 1:1 to PBT or photon RT from 18 to 25 UK RT centres, with PBT delivered in one of the two NHS proton centres, depending on geographical location with consideration for availability and photon RT delivered in the local RT centre. For participants allocated to PBT, the NHS will provide accommodation for preassessment visits and for the duration of PBT for the participant and one partner/caregiver. Following RT, all participants will receive adjuvant PCV chemotherapy at their local site. Follow-up will also be at local sites as per standard of care. Trial-specific participant assessments are summarised in table 2. The trial schema is shown in figure 2.

**Table 1 T1:** Inclusion and exclusion criteria

Inclusion criteria	Exclusion criteria
Histologically confirmed grade 2/3 ODG, 1p19q codeletion and IDH mutation	Leptomeningeal, spinal or infratentorial disease
Randomisation within 28 days of MRI which supports decision that RT is required at that point in time—outside of 28 days, an updated MRI is required	Prior cranial or head and neck RT
Aged 25 or over at start of RT	Previous chemotherapy for ODG. The use of vorasidenib or similar IDH inhibitors prior to radiotherapy, should these become available in the UK, will not render the patient ineligible
KPS≥70	Comorbid neurological condition(s) influencing NCF
Adequate wound healing/recovery following surgery (if applicable)	Contraindication to MRI or gadolinium
Able to provide study-specific written informed consent	Severe active comorbidity making patient unsuitable for radical RT and/or adjuvant chemotherapy
Able to complete baseline NCF testing in English	Any recognised genetic syndrome causing sensitivity to RT
Adequate haematological, renal and hepatic function for PCV chemotherapy	Contraindication to procarbazine, lomustine or vincristine, including coeliac disease and rare hereditary conditions of galactose intolerance, total lactase deficiency or glucosegalactose malabsorption
Able to swallow oral medication	Prior invasive malignancy, unless disease-free interval ≥3 years
Participants born female of childbearing potential must agree to be pregnancy screened prior to entering the trial, provide a negative pregnancy result within 7 days prior to randomisation and agree to use medically acceptable methods of contraception during RT, between the end of RT and start of adjuvant chemotherapy, during chemotherapy and for 6 months following the end of chemotherapy	Pregnancy or breastfeeding
Fertile participants born male must agree to use medically acceptable methods of contraception during RT, between the end of RT and start of adjuvant chemotherapy, during chemotherapy and for 6 months following the end of chemotherapy	Participant unable or unwilling to attend for follow-up
	Recognised genetic syndrome causing sensitivity to radiotherapy

IDHisocitrate dehydrogenaseKPSKarnofsky Performance StatusNCFneurocognitive functionODGoligodendrogliomaPCVprocarbazine, lomustine and vincristine chemotherapyRTradiotherapy

**Table 2 T2:** Schedule of assessments

	Baseline/pretreatment			Treatment	Post-RT follow-up							
	Eligibility/preregistration	Prerandomisation	Pre-RT	Weekly RT	1 month	3 months	6 months	1 year	2 years	3 years	4 years	5 years
Medical history	X											
Clinical assessment	X			X	X	X	X	X	X	X	X	X
Pregnancy test	X	X	X		X	X	X					
Informed consent	X											
MRI scan	X		X			X	X	X	X	X	X	X
Radiotherapy planning CT scan			X									
PBT or photon RT				X								
PCV chemotherapy						6×6-weekly cycles of adjuvant PCV chemotherapy						
Neurocognitive function tests*		X			X			X	X	X	X	X
CTCAE toxicity assessment		X		X	X	X	X	X	X	X	X	X
Endocrine assessments			X				X	X	X	X	X	X
HRQoL†		X		X‡	X	X	X	X	X	X	X	X
Work and economic impact§		X		X‡	X	X	X	X	X	X	X	X
Caregiver distress¶		X		X*‡	X	X	X	X	X	X	X	X

* EORTC core CTB COMP and CNS Vital Signs test battery.

† EORTC QLQ-C30 and BN20, EQ-5D-5L, MFI, HADS.

‡ Once in the final week of RT.

§ WPAI: General Health Questionnaire and health resource use questionnaire.

¶ Caregiver needs screen.

CNScentral nervous systemCTCAECommon Terminology Criteria for Adverse EventsEORTC CTB COMPEuropean Organisation for Research and Treatment of Cancer Core Clinical Trial Battery CompositeEORTC QLQ-C30 and BN20European Organisation for Research and Treatment of Cancer Quality of Life Questionnaire and Brain Neoplasm QuestionnaireEQ-5D-5LEuroQol-5 Dimension-5 Response-Level QuestionnaireHADSHospital and Anxiety Depression ScaleHRQoLhealth-related quality of lifeMFIMultidimensional Fatigue AssessmentPBTproton beam therapyPCVprocarbazine, lomustine and vincristineRTradiotherapyWPAIWork Productivity and Activity Impairment

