### Radiotherapy

The *APPROACH RT guidelines* provide full details on immobilisation, planning image acquisition, target volume and organ at risk contouring, treatment planning, treatment delivery and quality assurance.

RT will ideally start within 6 weeks of randomisation (and must start within 10 weeks). A dedicated MRI scan to assist in RT planning is mandated. The immediate postoperative MRI must not be used for this purpose, as post-operative changes may not have had sufficient time to resolve.

Total RT dose will be 54 Gy (RBE, relative biological effectiveness) in 30 daily 1.8 Gy fractions over approximately 6 weeks for grade 2 ODG and 59.4 Gy (RBE) in 33 daily 1.8 Gy fractions over approximately 6.5 weeks for grade 3 ODG. RBE-weighted dose in units of Gray (Gy (RBE)) will be used to describe the product of the absorbed dose and the RBE. The RBE will be interpreted as 1.1 for PBT and 1.0 for photon RT.

RT will be delivered as an outpatient on weekdays. Photon RT will be delivered using intensity-modulated RT or volumetric-modulated arc therapy. PBT will be delivered using pencil beam scanning, typically performed with single-field optimisation. Each participant treated using PBT will have an equivalent photon RT plan produced for use in the event of PBT machine problems.

For photon RT, local practice for treatment verification will be followed. For PBT, daily online image-guided verification with positional correction using 2D kV imaging or cone beam CT will be performed.

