### Chemotherapy

Adjuvant PCV chemotherapy is per standard of care, which in the UK is usually according to the BR12 trial schedule.^19^ Chemotherapy should start within 4–8 weeks of completion of RT. Initial doses (in the absence of renal or hepatic impairment) will be as follows:

Procarbazine 100 mg/m^2^, with dose banding/capping as per the institution’s usual practice one time per day on days 1–10 or days 2–11, orally, on a 42 day cycle, for up to six cycles.Lomustine 100 mg/m^2^, with dose banding/capping as per the institution’s usual practice day 1, orally, on a 42 day cycle, for up to six cycles.Vincristine 1.4–1.5 mg/m^2^ (or flat dose of 2 mg if this is usual institutional practice), with dose banding/capping as per the institution’s usual practice, intravenously, day 1, on a 42 day cycle for up to six cycles.

Suggested dose modifications and reductions are provided in the APPROACH trial protocol regarding PCV in the presence of haematological, pulmonary or neurological toxicity or renal or hepatic dysfunction.

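### Contraception for participants born female of childbearing potential is required only from the start of RT, leaving up to 10 weeks after randomisation uncovered (minor safety point)

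*Protocol article*

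**What the plan says.** Table 1 of the protocol article (Study design) requires participants born female of childbearing potential to "provide a negative pregnancy result within 7 days prior to randomisation and agree to use medically acceptable methods of contraception during RT". The same criterion continues the list with the periods "between the end of RT and start of adjuvant chemotherapy, during chemotherapy and for 6 months following the end of chemotherapy". The periods are named one by one, and the first is RT itself.

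The Radiotherapy section sets the start of treatment: "RT will ideally start within 6 weeks of randomisation (and must start within 10 weeks"). RT is given in "fractions over approximately 6 weeks for grade 2 ODG" and in "fractions over approximately 6.5 weeks for grade 3 ODG". The Chemotherapy section adds: "Chemotherapy should start within 4–8 weeks of completion of RT".

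Table 2 has a row headed "Pregnancy test". It is marked at eligibility/preregistration, prerandomisation and pre-RT, and then at 1, 3 and 6 months post-RT. It is not marked in the weekly RT column. Pregnancy and breastfeeding are exclusion criteria in Table 1.

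**The concern.** The two halves of the criterion are anchored to different dates: the negative test to randomisation and the contraception agreement to the start of RT. RT may begin weeks after randomisation, and nothing else in the article requires contraception in between.

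Two consequences follow, both minor and both about patient safety.

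- A pregnancy found at the pre-RT test would probably delay treatment in someone enrolled on an MRI that "supports decision that RT is required at that point in time".
- A conception too recent for that test to show could pass through the whole RT course before the next scheduled test.

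The point concerns only participants born female of childbearing potential. It makes no claim about the criterion for male participants or about pregnancy testing during PCV.

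**Working it through.** There is no figure in the plan to reproduce. The check sets the stated periods side by side and adds the stated time limits.

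**Inputs**

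- Qualifying negative test: up to 7 days (1 week) before randomisation (Table 1).
- Randomisation to RT start: up to 6 weeks ideally, 10 weeks at most (Radiotherapy).
- RT duration: about 6 weeks for grade 2 and about 6.5 weeks for grade 3 (Radiotherapy).
- End of RT to chemotherapy: 4 to 8 weeks (Chemotherapy).
- Tests after the pre-RT one: the first is at 1 month post-RT (Table 2).
- Assumption: 1 month = 30.4 days, so 30.4 / 7 = 4.34 weeks.

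**Which periods the agreement covers**

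| Period | Length | In the Table 1 list? |
|---|---|---|
| Randomisation to RT start | up to 6 weeks ideally, 10 at most | No |
| RT | about 6 to 6.5 weeks | Yes |
| End of RT to chemotherapy | 4 to 8 weeks | Yes |
| Chemotherapy | up to six 42-day cycles | Yes |
| After chemotherapy | 6 months | Yes |

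**Uncovered interval, counted from the qualifying test**

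- Ideal limit: 6 + 1 = 7 weeks.
- Maximum: 10 + 1 = 11 weeks.

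**From RT start to the next scheduled pregnancy test**

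- Grade 2: 6 + 4.34 = 10.3 weeks.
- Grade 3: 6.5 + 4.34 = 10.8 weeks.

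This second interval is not a period without contraception, because the agreement applies throughout it. It shows how long a conception that occurred just before RT, and was missed by the pre-RT test, could go without another scheduled test.

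**What the pre-RT test does.** It falls inside the uncovered interval and should find most conceptions there before any RT is given. It cannot prevent a conception, and a very recent one may not yet show. The article does not say how close to the first fraction the test must be.

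**The case against.** The strongest reply is that the contraception window follows exposure. No trial RT or PCV is given between randomisation and RT, and cover is continuous from the first fraction to 6 months after chemotherapy. On that view the treatment-free weeks between RT and chemotherapy belong in the window because they lie between two exposures, whereas the weeks before RT do not. This is a coherent reading, and the comparison between the two gaps is therefore not exact. It does not settle the matter, because a conception shortly before RT can still be exposed to RT, and contraception that begins with RT comes too late for it.

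A second reply is that the interval is already controlled by the pre-RT test. That is largely true and is the reason the point is minor. What remains is prevention, and the very recent conception that the test may miss.

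A third is that the full protocol, the RT guidelines and the Participant Information Sheet are not shown and may give earlier advice or fix the test's timing. They may. The point rests on what the published criterion states: a list with a defined start and end, and not a summary that leaves the period open.

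It is also fair to say that the MRI wording concerns how recent the imaging is rather than how much delay is tolerable, and that the plan itself accepts up to 10 weeks. Any harm from delay should therefore not be overstated.

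**Conclusion.** The point holds as a minor patient-safety improvement. As published, the criterion leaves up to 6 weeks ideally, and 10 weeks at most, between randomisation and RT with no agreed contraception. The pre-RT test is the only safeguard stated for that interval. These are upper limits and not typical durations.

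The conclusion assumes that no document outside the article starts the agreement earlier. The size of the remaining risk is unknown: the article gives no frequency of conception in the interval and no basis for estimating how often the pre-RT test would miss one. Nothing here affects the sample size, power or alpha.

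**What to change.** In the Table 1 criterion for participants born female of childbearing potential, start the agreement at randomisation. The revised requirement would be: *contraception is to be used from randomisation, throughout RT, chemotherapy and the interval between them, and until 6 months after chemotherapy ends*. Keep the pre-RT test in Table 2, which then checks a precaution already in place. The criterion for male participants and the test schedule stay as they are.

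The cost is one phrase in one criterion and the matching line in the information sheet, made at the next amendment. Participants take on a contraception commitment longer by up to 6 weeks ideally and 10 weeks at most. No participants, visits or tests are added.

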**Figure 2 F2:**
[figure not shown]
Trial schema. HRQoL, health-related quality of life; IDH, isocitrate dehydrogenase; KPS, Karnofsky Performance Status; NCF, neurocognitive function; ODG, oligodendroglioma; OS, overall survival; PBT, proton beam therapy; PCV, procarbazine, lomustine and vincristine; PFS, progression-free survival; RT, radiotherapy.

The main trial analyses will be staged:

Stage 1: assessment of feasibility of recruitment (first 12 months)Stage 2: efficacy interim analysis of NCF (all participants at 2 years)Stage 3: futility interim analysis of NCF (50% of participants at 5 years)Stage 4: final analysis of NCF and secondary endpoints (all participants at 5 years)

The original planned start and end dates for the trial are 1 February 2021 to 17 July 2031. Recruitment commenced on 17 January 2024.

See ‘Statistical considerations’ section for further detail.

### Radiotherapy

The *APPROACH RT guidelines* provide full details on immobilisation, planning image acquisition, target volume and organ at risk contouring, treatment planning, treatment delivery and quality assurance.

RT will ideally start within 6 weeks of randomisation (and must start within 10 weeks). A dedicated MRI scan to assist in RT planning is mandated. The immediate postoperative MRI must not be used for this purpose, as post-operative changes may not have had sufficient time to resolve.

Total RT dose will be 54 Gy (RBE, relative biological effectiveness) in 30 daily 1.8 Gy fractions over approximately 6 weeks for grade 2 ODG and 59.4 Gy (RBE) in 33 daily 1.8 Gy fractions over approximately 6.5 weeks for grade 3 ODG. RBE-weighted dose in units of Gray (Gy (RBE)) will be used to describe the product of the absorbed dose and the RBE. The RBE will be interpreted as 1.1 for PBT and 1.0 for photon RT.

RT will be delivered as an outpatient on weekdays. Photon RT will be delivered using intensity-modulated RT or volumetric-modulated arc therapy. PBT will be delivered using pencil beam scanning, typically performed with single-field optimisation. Each participant treated using PBT will have an equivalent photon RT plan produced for use in the event of PBT machine problems.

For photon RT, local practice for treatment verification will be followed. For PBT, daily online image-guided verification with positional correction using 2D kV imaging or cone beam CT will be performed.

